### Objectives {7}

Aim 1: To determine the efficacy of mobile-based CBT interventions, compared with conventional interventions, in ASCVD patients receiving standard treatments;Hypothesis 1a (primary study hypothesis): a significant reduction in objective parameters, including LDL-C level, will be demonstrated in participants randomly assigned to the CBT group relative to participants in the conventional interventions group.

Aim 2: To improve our capacity to match patients to treatments more efficiently by identifying self-efficacy, and quality of life.Hypothesis 2a: a significant improvement in self-efficacy, and quality of life, measured by scales and questionnaires, will be demonstrated in participants randomly assigned to the CBT group relative to participants in the conventional interventions group.

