### Trial design {8}

This study is a multicenter, prospective, randomized, controlled, open-label parallel-group superiority trial. Patients will be randomly allocated at a 1:1 ratio to evaluate the efficacy of CBT to lower blood lipids in ASCVD patients. The study protocol follows the Standard Protocol Items: Recommendations for Interventional Trials (SPIRIT) [18].

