### Primary outcome measure

*LDL-C level*. The primary endpoint will be the mean change in LDL-C level [time Frame: from randomization (day 0) to V5 (week 24) for a total of 6 months of treatment]. Per guideline, the LDL-C level has been validated as a primary measurement for the clinical efficacy of the treatments [3].

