### Sample size {14}

Considering the primary outcome variable as the reduction in the mean LDL-C from baseline to week 24, an absolute reduction of 20% in LDL-C is expected [22, 23]. One hundred twenty-two subjects per group was calculated initially to offer 80% power at a one-sided 0.05 significance level according to a 1:1 ratio of random grouping. Allowing for a maximum follow-up loss rate of 20% in both groups, 300 patients were determined as the target sample size—150 patients in each group.

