### Statistical methods

#### Statistical methods for primary and secondary outcomes {20a}

Categorical variables will be expressed in numerical values with their respective percentages and compared using the chi-squared test at baseline. Continuous variables will be expressed as mean ± SD and compared using the *t*-test. The significance of primary and secondary endpoints will be evaluated with the paired-samples *t*-test. A *p*-value < 0.05 indicates statistical significance. All data will be analyzed with the SPSS.

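### The only test tied to the primary and secondary endpoints is a paired-samples t-test, which assesses change within an arm and not the CBT-versus-control contrast of the hypotheses

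*Protocol article*

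**What the plan says.** Statistical methods {20a} assigns a test to the endpoints in one sentence: "The significance of primary and secondary endpoints will be evaluated with the paired-samples" *t*-test. Two sentences come before it. One limits the chi-squared test for categorical variables to baseline. The other is general: "Continuous variables will be expressed as mean ± SD and compared using the" *t*-test, with no mention of endpoints, arms or visits. The section on additional analyses {20b} plans none.

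Trial design {8} describes an "open-label parallel-group superiority trial" with individual 1:1 randomisation, and no matching of patients appears anywhere. Objectives {7} words both hypotheses as between-arm contrasts: the effect "will be demonstrated in participants randomly assigned to the CBT group relative to participants in the conventional interventions group". The primary outcome section adds: "The primary endpoint will be the mean change in LDL-C level", from randomisation to week 24. The secondary list includes two percentages of participants meeting lipid thresholds, alongside a ratio to baseline, a coefficient of variation, CRP, BMI and two scale scores.

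**The concern.** Patients in the two arms are independent, so there is no pair to form across arms. A paired test on LDL-C compares week 24 with day 0 in the same patients. Its null hypothesis is no change over time in that arm, whereas Hypothesis 1a concerns a difference between arms.

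The distinction matters here because LDL-C could fall in both arms without any CBT effect. Both arms receive standard drug treatment, controls receive education on lifestyle and drug use at each follow-up visit, and time and regression to the mean act on everyone. A within-arm test attributes all of that to CBT. Setting the two arms' paired tests beside each other, significant in one and not in the other, is not a valid comparison either.

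The same sentence covers the two percentage endpoints, which are yes/no for each patient. A paired *t*-test is not suited to them, and chi-squared is named only for baseline.

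**Working it through.** **1. Which contrast the named test addresses**

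| Item | Source | Contrast |
|---|---|---|
| Hypotheses 1a, 2a | Objectives {7} | CBT versus control |
| Design | Trial design {8} | two independent arms, no matching |
| Test tied to endpoints | Statistical methods {20a} | follow-up versus baseline, same patient |
| General *t*-test sentence | Statistical methods {20a} | not stated |
| Further analyses | {20b} | none |

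This comparison carries the point and needs no arithmetic. The rest illustrates size.

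**2. The plan's own figure**

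Sample size {14} gives 122 per group, 80% power and one-sided 0.05, with the statement that "an absolute reduction of 20% in LDL-C is expected". It gives no SD and does not say whether the 20% is within or between arms, so 122 can be neither reproduced nor refuted. Solving backwards with the two-sample formula:

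- d = (z₀.₉₅ + z₀.₈₀) × √(2/122) = 2.486 × 0.1280 = 0.318
- if 20 percentage points is the between-arm difference, SD = 20/0.318 ≈ 63 points

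SD 63% is therefore one value consistent with the plan, on that reading only. SD 30% is a lower assumed value for contrast. The 20% loss allowance leaves 150 × 0.8 = 120 per arm.

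**3. No CBT effect, both arms fall by 10% (assumed)**

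One-sample noncentral *t*, n = 120, two-sided 0.05, critical value 1.980, noncentrality (10/SD) × √120. With independent arms and the same probability p in each, significant in CBT but not in control has probability p(1 − p).

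| SD of change | Noncentrality | p: CBT-arm paired test significant | p(1 − p) |
|---|---|---|---|
| 30% | 3.65 | 0.952 | 0.952 × 0.048 = 4.6% |
| 63% | 1.74 | 0.407 | 0.407 × 0.593 = 24% |

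The last column cannot exceed 25%, so 24% is close to the worst case. At SD 30% it is small because both arms are nearly always significant. At the one-sided 0.05 of the sample-size section, the CBT-arm figures are 98% and 53%.

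**4. Simulation check**

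10,000 runs, 122 per arm, the same true fall in both arms, two-sided 0.05, counting significant falls for the paired tests:

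| Shared fall (SDs of change) | CBT-arm paired test | CBT significant, control not | Independent-samples test on change |
|---|---|---|---|
| 0 | 2.6% | 2.5% | 4.9% |
| 0.1 | 19% | 15% | 5.0% |
| 0.2 | 59% | 25% | 5.2% |
| 0.3 | 91% | 8.4% | 4.5% |
| 0.5 | >99.9% | 0.03% | 4.7% |

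The between-arm test holds its level whatever the shared fall. The within-arm test does not.

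**5. Precision of the replacement**

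If baseline and week-24 variances are equal with correlation r, the variance of the ANCOVA estimate relative to an unadjusted change score is (1 − r²)/(2(1 − r)) = (1 + r)/2. That is 0.65 at r = 0.3 and 0.85 at r = 0.7 (assumed range).

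**The case against.** The strongest defence is the general *t*-test sentence. The limit to baseline stands only in the chi-squared sentence, so the *t*-test sentence could be read as a comparison of the arms throughout. The abstract also speaks of comparing LDL-C with a control group and of measures between the two groups at each visit. A reader might infer from the paired-test sentence that the trial will make no between-arm comparison at all. That is stronger than the article supports, because the intention to compare arms is visible. The defence does not remove the problem, however. The general sentence does not mention endpoints, and the next sentence gives the endpoints expressly to the paired test. On the kindest reading two tests compete for the primary endpoint, and the explicit one does not fit the hypothesis.

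Three further inferences should be resisted:

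- Baseline LDL-C is not left unused. The primary endpoint is change from baseline, and a paired test uses baseline directly. Preferring ANCOVA to a change score is a matter of efficiency, not the correction of an error.
- The ratio to baseline is not untestable within patients. It can be tested against 1 or on the log scale. The valid objection is that such a test is still within-arm.
- The percentages above are not predictions. The article gives neither an SD nor an expected control-arm change. Patients must already be on statins at entry, so a large shared fall from starting a statin should not be presumed.

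The choice of test cannot be excused as something left to an analysis plan, since the article names the test.

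**Conclusion.** The sentence is wrong as written and must be corrected. It ties the endpoints to a within-arm test, while the hypotheses and design call for a between-arm one. It also applies a paired *t*-test to two binary endpoints for which no follow-up test is otherwise named. This conclusion rests on the text alone.

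The size depends on assumptions. With no CBT effect and an assumed shared fall of 10%, a claim based on the CBT arm alone would be made in 41% to 95% of trials. A claim based on discordant arms would be made in 4.6% to 24%. A between-arm test errs in about 5%. With no shared fall, the CBT-arm test shows a significant reduction in only about 2.6%, so the harm grows with the fall common to both arms. No corrected sample size follows, because no SD is given.

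**What to change.** Replace the paired-test sentence with: *The primary analysis is the between-arm difference in LDL-C change from baseline to week 24, with 95% CI, from ANCOVA adjusted for baseline LDL-C. Continuous secondary endpoints are compared between arms in the same way, using the baseline value where one exists. Percentage endpoints are compared between arms with a method for binary data (e.g. chi-squared or logistic regression). Within-arm changes are descriptive only.*

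An independent-samples *t*-test on change would also be valid. ANCOVA is normally more precise, and one method should be fixed as primary.

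One linked change is needed. The section on non-adherence and missing data {20c} bases the primary analysis on a full analysis set defined by having received CBT for at least 4 weeks. Read literally this contains no controls, so the definition must include them before a between-arm analysis can be run.

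The cost is a protocol amendment through the steering committee and the ethics committee, as section {25} provides. Trial status reports recruitment complete in January 2022, but no new data or patients are required, and the analyses run in SPSS.

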#### Interim analysis {21b}

There will be no interim analysis.

#### Methods for additional analysis (e.g., subgroup analysis) {20b}

No additional analysis will be conducted.

#### Methods in analysis to handle protocol non-adherence and any statistical methods to handle missing data {20c}

All patients who have received CBT for at least 4 weeks will be included in the full analysis set (FAS). Depending on the time investigated, the per-protocol (PP) analysis set will be made up of patients who complete the 6-month follow-up examinations. The FAS will be used as the basis for the primary analysis. If there is a discrepancy of greater than 10% between the FAS and PP samples, the analysis will be repeated for the PP analysis set. The safety population will include patients in the FAS. Unless otherwise noted, all analysis will be done in both the FAS and PP analysis sets.

There will be no replacement or imputation of missing values. All analysis will be based solely on observed cases. Patients who are loss to follow-up will be considered to have dropped out of therapy. Only the PP patients will be used in a sensitivity analysis to test the impact of this assumption.

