### Interventions

#### Explanation for the choice of comparators {6b}

A control intervention—conventional lifestyle intervention—will be provided to help compare the effects of CBT in ASCVD patients. The control group will receive patient education delivered with oral communications given by healthcare providers. Patient education including disease-related knowledge, lifestyle guidance, complication prevention, rational drug use, and other contents will also be delivered to the control group. Patient education will be delivered only during each follow-up. Both the intervention group and the control group will receive standard pharmacological treatments.

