#### Criteria for discontinuing or modifying allocated interventions {11b}

Discontinuation from the treatment program will be considered in the following conditions. Participants will not be considered to have dropped out of the experiment at this point, and they will be eligible to receive protocol assessments unless they withdraw their consent for assessments (as described below):If the participant wishes to stop the protocol treatment;If the participant is unable to continue the protocol treatment due to adverse events;When the investigator believes that the risk of continuing the protocol treatment outweighs the benefit for any reason;When the investigator believes that continuing the protocol treatment is not appropriate for any other reason.

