### Assignment of interventions: blinding

#### Who will be blinded {17a}

Participants and investigators will be aware of the intervention that has been assigned to them in this open-label trial. Because of the nature of the patient-reported outcome measures, not all outcome evaluations will be blinded. During the analysis, the statistician will be blinded to the allocation.

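### The full analysis set behind the primary analysis requires at least 4 weeks of CBT, so as worded it contains no controls, and on a lenient reading it drops early stoppers from the CBT arm only

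*Protocol article*

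**What the plan says.** All the analysis sets are defined in section {20c} of the protocol article:

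- Full analysis set: "All patients who have received CBT for at least 4 weeks will be included in the full analysis set (FAS").
- Its role: "The FAS will be used as the basis for the primary analysis".
- Safety set: "The safety population will include patients in the FAS".
- Per-protocol set: "the per-protocol (PP) analysis set will be made up of patients who complete the 6-month follow-up examinations".
- Missing data: "All analysis will be based solely on observed cases".

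The comparator is described in section {6b}: "The control group will receive patient education delivered with oral communications given by healthcare providers". Objectives {7} and Trial design {8} set out a 1:1 randomised, parallel-group superiority comparison of CBT with conventional intervention. Section {11b} says of patients who stop the programme: "Participants will not be considered to have dropped out of the experiment at this point". They remain eligible for assessment unless they withdraw consent for it.

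No intention-to-treat or all-randomised set appears in the article.

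**The concern.** A full analysis set should keep the groups that randomisation created. This one is defined by exposure to the experimental treatment, which controls never receive. Taken at its word, the primary analysis has one arm.

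The natural repair by a reader is to keep all controls and apply the 4-week condition to the CBT arm. That gives a comparison, but not the randomised one. Patients who give up early are removed from one side, and the control patients who would have done the same remain. The article's own background section says that poor compliance limits lipid lowering, so the removed patients plausibly have worse LDL-C results. The likely bias therefore favours CBT. The trial is also open-label, so the decision to continue is made knowing the allocation.

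The safety population inherits the same restriction. As worded it has no controls either, and it omits CBT patients who stop before 4 weeks, including any who stop because of an adverse event.

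**Working it through.** **1. Who can enter the FAS as worded.** The condition is at least 4 weeks of CBT. Planned size is 150 per arm (Sample size {14}).

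| Arm | Intervention | Can meet the condition |
|---|---|---|
| CBT | App-based CBT | at most 150 |
| Control | Oral education at follow-up visits | 0 |

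With no controls, a between-arm difference does not exist. This step needs no assumption.

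**2. What the planned sample size implies.** Section {14} gives 122 per group, 80% power, one-sided 0.05 and a 20% reduction, but no SD, so the 122 cannot be reproduced directly. Solved backwards:

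d = (1.645 + 0.842) × √(2/122) = 0.318 SD

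If the 20% is a difference of 20 percentage points, the implied SD is 20/0.318 ≈ 63 points. (At two-sided 0.05, d = 0.359 and the SD is about 56.) Inflating for 20% loss gives 122/0.80 = 152.5, so 153 against the stated 150, a negligible gap.

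**3. Lenient reading: all controls kept, CBT arm restricted to those who persist.** Assumptions, none of them from the documents: no true CBT effect; a share q of either arm is of the early-stopping type; such patients have an LDL-C change 20 points worse; all retained patients have a week-24 value; two-sample test.

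- Bias = q × 20: 0.10 × 20 = 2 points; 0.20 × 20 = 4 points.
- Share of the 20-point target: 2/20 = 10%; 4/20 = 20%.
- Standard error = SD × √(1/[150(1 − q)] + 1/150).
- False-positive rate favouring CBT = 1 − Φ(c − bias/SE), with c = 1.96 (nominal 2.5%, the upper half of two-sided 0.05) or c = 1.645 (one-sided 0.05, as in section {14}).

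| SD | q | Bias | SE | Bias/SE | Nominal 2.5% becomes | Nominal 5% becomes |
|---|---|---|---|---|---|---|
| 30 | 0.10 | 2 | 3.56 | 0.56 | 8.1% | 14% |
| 30 | 0.20 | 4 | 3.67 | 1.09 | 19.2% | 29% |
| 63 | 0.10 | 2 | 7.47 | 0.27 | 4.5% | 8% |
| 63 | 0.20 | 4 | 7.72 | 0.52 | 7.5% | 13% |

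A simulation with 150 per arm and a two-sided 0.05 t-test gave 8.3%, 19.2%, 4.4% and 7.2% for the four rows.

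**4. Wider range, in SD units.** For q from 0.1 to 0.3 and a gap g of 0.25 to 0.75 SD, bias = q × g runs from 0.025 to 0.225 SD, and the one-sided error at nominal 5% runs from 7.6% to 54.9%. A middle case, q = 0.2 and g = 0.5, gives 0.10 SD. That is 0.10/0.318 = 31% of the implied effect, with an error rate of 20.4%.

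**5. Fit with section {11b}.** A CBT patient who stops in week 3 but attends week 24 is assessed under {11b}, yet is left out of the primary analysis under {20c}. The two sections pull against each other: the data are collected and then not used where they matter most.

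**The case against.** The best defence is that CBT is a slip for the allocated intervention. The objectives and design plainly intend a between-arm comparison, control education is given at follow-up visits, and the first of these is at 1 month, so a 4-week rule could be meant for both arms. On that reading a bias toward CBT no longer follows automatically. That much stands: the direction is then uncertain. But the text does not say this. Membership would also still depend on exposure after randomisation, and the exposures are not alike, being scheduled app sessions in one arm and visit-based education in the other.

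Second, the per-protocol set carries no CBT condition and could include controls, so some comparison survives. True, but it is restricted to completers and is not the primary basis. As written it is not even a subset of the FAS.

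Third, the magnitude is illustrative. The assumed 20-point gap equals the whole target effect, and stopping an app does not mean stopping statins. With observed cases only, some early stoppers would be missing from both arms anyway. If half of them were, the stopper share left among controls would be 0.05/0.95 to 0.10/0.90, the bias about 1.1–2.2 points, and the nominal 2.5% would become roughly 5–9% at SD 30 and 3–5% at SD 63. Section {20a} also names a paired test for the endpoints, so these rates are not those of the stated test. All of this is fair, and it bears on the size only.

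Fourth, section {17a} says "During the analysis, the statistician will be blinded to the allocation". Building an arm-dependent set need not break this, because a data manager could flag membership and pass on masked codes. The blinding aspect is minor. Likewise {11b} says who is assessed, not who is analysed, so tension is a better word than contradiction.

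**Conclusion.** The concern holds and must be fixed before the data are analysed. As worded, the primary analysis set has 0 of 150 controls; that follows from the text alone. On the lenient reading the comparison exists but is no longer the randomised one, and it probably favours CBT: a spurious 2–4 points, and a false-positive rate of about 8–19% (SD 30) or 4.5–7.5% (SD 63) in place of 2.5%. Those figures rest on an assumed 10–20% early-stopping share and an assumed 20-point gap, and are smaller if many early stoppers have no week-24 value. Even the most generous reading selects patients on what happened after randomisation. This is a rule that the article states and fixes, not a detail left to a separate analysis plan.

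**What to change.** Replace the FAS sentence in section {20c} with: *The FAS comprises all randomised participants, analysed in the arm to which they were allocated, regardless of CBT received or discontinued.* Keep this set for the primary analysis, and move the 4-week exposure rule to a supplementary analysis labelled as such. Because the safety population is tied to the FAS, the same change brings controls and early stoppers into it; confirm that this is intended.

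The cost is one sentence. No extra patients or visits are needed, since {11b} already provides for assessing patients who stop. The estimate may be somewhat smaller because early stoppers count. Power is hardly affected: with 20% loss, 150 × 0.80 = 120 per arm are observed, and Φ(0.318 × √60 − 1.645) = 79.4% at one-sided 0.05, against the planned 80%.

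The change does not recover missing week-24 values. While the observed-cases rule stands, patients without a week-24 LDL-C still drop out of the estimate, and that needs its own answer.

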#### Adverse event reporting and harms {22}

The type and frequencies of any adverse event will be reported to the Chinese National Adverse Reaction Monitoring Center. Any trial deviations and violations will also be sent to the Chinese National Adverse Reaction Monitoring Center.

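### The safety population is defined only through a full analysis set that requires 4 weeks of CBT, so CBT patients who stop sooner, including for adverse events, fall outside it

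*Protocol article*

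**What the plan says.** Two rules in the protocol article's section on non-adherence and missing data {20c} have to be read together. The first sets the analysis population: "All patients who have received CBT for at least 4 weeks will be included in the full analysis set (FAS"). The second sets the safety population by reference to it: "The safety population will include patients in the FAS". The same section makes the FAS the main efficacy set: "The FAS will be used as the basis for the primary analysis". The only other set it defines is the per-protocol set, made up of those who complete the 6-month examinations; it is not named as a safety set.

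Three other sections bear on the point:

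- Criteria for discontinuing {11b} lists among the reasons for stopping: "If the participant is unable to continue the protocol treatment due to adverse events". It sets no minimum time on treatment. Of those who stop it says: "Participants will not be considered to have dropped out of the experiment at this point".
- Choice of comparators {6b} describes the other arm: "The control group will receive patient education delivered with oral communications given by healthcare providers". Controls receive no CBT.
- Adverse event reporting {22} says: "The type and frequencies of any adverse event will be reported to the Chinese National Adverse Reaction Monitoring Center".

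**The concern.** A safety set should hold everyone who was exposed, however briefly. Here entry is earned by 4 weeks of exposure. Someone who stops in week 2 because of an adverse event is among the most informative patients for safety, and the rule removes that patient. Selection is then partly on the outcome being measured. The 4-week threshold also falls early in the programme, in or next to what the intervention description {11a} calls the strong intervention period.

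What is at stake is the adverse event table of the final report: the CBT-arm frequencies may be too low and, on the literal wording, there is no control column to set beside them. This is not detail left to an analysis plan. The article states the rule, and the rule as stated gives the wrong population.

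**Working it through.** **Inputs.** Target of 300, 150 per arm; 122 per group before loss; maximum loss 20% (Sample size {14}). FAS and safety rules from {20c}. No early-stopping rate and no adverse event rate appear in the article, so both are assumed below and shown as ranges.

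**The plan's own figure.** 122 / (1 − 0.20) = 152.5, so 153 per group; 122 × 1.20 = 146.4, so 147 per group. The stated 150 lies between the two and is accepted as the number randomised per arm. Nothing below depends on how the 122 was reached.

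**Step 1: who is in the safety set as written.**

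- CBT patient, 4 weeks or more of CBT: in the FAS, in the safety set. This includes anyone who stops for an adverse event after week 4.
- CBT patient, less than 4 weeks, any reason for stopping: not in the FAS, and in no named safety set.
- Control: receives no CBT, so cannot meet the FAS condition as worded.

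**Step 2: how many CBT patients are dropped.** Dropped = 150 × w, where w is the assumed share stopping before week 4.

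| w (assumed) | dropped | CBT patients left |
|---|---|---|
| 5% | 7.5, about 8 | 142 |
| 10% | 15 | 135 |
| 20% | 30 | 120 |

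**Step 3: the direction of the error.** Let E be the share of early stoppers with an event and L the share among the remaining CBT patients. The frequency in the whole CBT arm is w·E + (1 − w)·L. The reported frequency is L. The error is L minus that sum, which equals w·(L − E). It is negative (understatement) when E exceeds L, zero when they are equal, and positive when E is below L.

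With L = 10% (assumed), the reported figure is always 10.0%. The whole-arm figure would be:

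| w | every early stopper had an event (E = 100%) | none did (E = 0) |
|---|---|---|
| 5% | 0.05 + 0.95 × 0.10 = 14.5% | 0.95 × 0.10 = 9.5% |
| 10% | 0.10 + 0.90 × 0.10 = 19.0% | 0.90 × 0.10 = 9.0% |
| 20% | 0.20 + 0.80 × 0.10 = 28.0% | 0.80 × 0.10 = 8.0% |

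These are the extremes. Because adverse events are one of the listed reasons for stopping, E above L is the more plausible side, and the possible error is much larger on that side.

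**Step 4: does another section repair it?** Section {22} requires notification to a national center with no 4-week condition, but names no analysis set or denominator. Section {11b} keeps those who stop under assessment, so their data can exist, but it does not put them in the safety set. Neither changes the rule.

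**The case against.** The strongest reply is that this is the FAS problem seen a second time. If the FAS were corrected to all randomised participants, the safety sentence would follow and yield the population asked for here. That is right as far as it goes. But the article does not define the FAS that way, and a corrected FAS that kept any minimum exposure would bring the safety problem back.

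Several stronger readings are tempting, and the article does not support them:

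- *Safety is equated with the FAS.* The sentence says that the set includes FAS patients. Since no other members are named, the FAS is the only working definition, but equality is not stated.
- *Half the trial, 150 of 300, is deliberately left out of safety.* That is the literal result. Yet the same FAS is to carry the primary comparison of a 1:1 two-arm trial {8}, which cannot be run without controls. A drafting slip is the likelier explanation.
- *Early events are lost, or early stoppers count as event-free.* Neither follows. The events are still notified under {22}, and the patients leave numerator and denominator together.
- *Frequencies are understated by construction.* Section {11b} also allows stopping at the participant's wish or on the investigator's judgement, so event-free patients are dropped too, and the error can run either way.

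It is also fair to say that the practical weight is limited. The article calls the intervention low-risk {21a} and unlikely to cause harm {30}, and lists no adverse event measure among its outcomes. That lowers the priority. It does not justify a set that can remove the patients who would test the assumption.

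**Conclusion.** The point holds for CBT patients who stop before week 4: as written they are outside the safety analysis, whatever made them stop. Adverse event frequencies in that arm are therefore likely, but not certain, to be too low. For assumed early stopping of 5% to 20%, about 8 to 30 of 150 patients are affected; the article gives no rate against which to judge that range.

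For controls, the literal text leaves no between-arm safety comparison. This should be raised as a probable slip to be corrected, not as the size of the finding. The obvious repair, a 4-week rule in each arm, would leave the main point standing.

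The change should be made, with moderate priority. The efficacy conclusions do not depend on it.

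**What to change.** Replace the safety sentence in {20c} with:

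> The safety population comprises all randomised participants in both arms, analysed by the intervention actually received, with no minimum duration of exposure; adverse events from randomisation to week 24 are reported by arm.

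If the FAS is corrected to all randomised participants, the two populations will coincide. The safety sentence should still state that there is no minimum exposure, so that it does not depend on how the efficacy set is worded.

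The cost is one sentence. No extra visits are needed for those who stop treatment, because {11b} keeps them eligible for assessments unless they withdraw consent. One thing to confirm is that adverse events are recorded in the same way in both arms; the article does not describe how they are collected.
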